#### Management of suicidality

1.3.1

Due to the phasic nature of depressive disorders, worsening of symptoms may occur during study participation, including the occurrence of suicidal thoughts. Participants are required to be in treatment for their depression (see Table 1) as there will be no treatment or continuous, face-to-face monitoring of suicidality through the study centre. However, the weekly self-report of depressive symptoms (see Measures) includes one item assessing suicidal thoughts. During the monthly appointments, the participants’ answers to this item are reviewed. In case that a participant has indicated the presence of suicidal thoughts on more than half of the days or almost every day during the last week (item 9 ≥ 2) on one or more occasions, the project leader is informed and participants are encouraged to either contact their attending physician or psychotherapist, the nearest outpatient clinic of a psychiatric clinic, or the psychiatric emergency department. If the study participation cannot be continued safely, termination of the participation is discussed with the participant.

#### Premature study termination (dropout)

1.3.2

Participation in the study is voluntary. Participants can decide to opt-out of the study at any time without providing any reasons. In case that the participation of a participant ends prematurely, all procedures of V12 are brought forward to a final assessment. If a participant is not able to complete V12, only a short meeting is scheduled to return the smartwatch and complete the BDI-II questionnaire.

#### Trial status

1.3.3

Recruitment started in August 2023, first patient in was September 27, 2023, last patient out was December 02, 2024.

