### Design

1.1

This exploratory study uses an observational n-of-1 design [36], involving repeated measurements of self-reported, behavioural, and physiological outcomes over the time of one year (365 days) within individuals without manipulation of variables by the investigators. The work is carried out in accordance with the World Medical Association Declaration of Helsinki [37]. Ethical approval has been granted by the Ethics Committee of the Department of Medicine at Goethe University Frankfurt, Germany (date: 24/08/2023, reference number: 2023–1309). The study protocol has been registered in the German Clinical Trials Register (reference number: DRKS00032618).

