### Study population

1.2

We aim to collect 10–12 complete case studies of adult patients with depressive disorders; allowing for some dropout, *N* = 15 participants will be included. Patients are recruited at the Department of Psychiatry, Psychosomatic Medicine and Psychotherapy, University Hospital of Goethe University Frankfurt, Germany. This study protocol is presented to treating physicians and psychologists at various occasions and a flyer with the inclusion and exclusion criteria (see Table 1) is provided. Physicians and psychologists invite patients who are receiving treatment for affective disorders to participate in the current study. Interested patients provide their contact details and written consent to be contacted by the study centre. If sufficient participants can't be reached, various communication channels of the German Foundation for Depression and Suicide Prevention (e.g., newsletter, website, online discussion forum) shall be used to draw the attention of interested participants to the study.

**Table 1 tbl1:** Inclusion and exclusion criteria for study participation.

Inclusion criteria	Exclusion criteria
- Minimum 18 years old	- Acute risk of self-hazard/suicidality (six months before inclusion)
- Diagnosis of a recurrent major depression (ICD-10 F33) with two or more depressive episodes during the last ten years	- Currently severe depressive episode with psychotic symptoms (F33.3)
- Currently residual symptoms of depression (BDI-2 sum score ≥14)	- Lifetime diagnosis of any psychotic disorder (any diagnosis according to ICD-10 F2)
- Being in concurrent treatment for the depressive illness	- Lifetime diagnosis of any bipolar disorder (ICD-10 F31)
- Being able to provide informed consent	- Lifetime diagnosis of any borderline personality disorder
- Usage of an own Android smartphone (or agreement to switch to an Android smartphone provided by the study centre)	- Severe somatic illnesses requiring intensive treatment
- In case of any lifetime substance abuse disorder: being in stable remission (min. 6 months)	

Note: ICD-10 = International Classification of Diseases, Tenth Revision, BDI-2 = Beck Depression Inventory-II.

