**Fig. 1 fig1:**
[figure not shown]
Timeline of study procedures. Caption: At baseline (V0, time requirement: 3.5–4 h), participants read the participant information sheet, clarify any questions about the study with the study team, and provide written, informed consent for study participation. A standardized clinical interview (SCID-5) is conducted and several self-report questionnaires are filled in (see Measures section). After the assessments are completed, the participants are assisted in installing the iTrackDepression-App (iTD-App) via the Google PlayStore on their smartphone. The iTD-App has been developed by the German Foundation for Depression and Suicide Prevention in collaboration with adesso SE (Dortmund, Germany) and the InfAI Institute for Applied Informatics (Leipzig, Germany). It has two major components for the collection of depression-related data: self-report assessments and sensor technology. Additionally, participants are asked to continuously wear a Samsung Galaxy 5® smartwatch that is provided by the study centre to record data on physiological and behavioural parameters such as heartbeat and physical activity (please refer to Measures for a detailed description). Any technological questions are clarified before the participants start continuous data collection in their daily lifes. V1-V5 and V7-V11 are used to provide technical support, check for data completeness, and manage suicidality if necessary. These appointments can be conducted via video call or telephone, depending on the preference of the participants. At V6 (6-month follow-up), the BDI-II will be completed at the study centre and any changes in the treatment plan during the last six months are assessed. The final appointment (V12) is conducted after 12 months of study participation. At V12, the SCID-5 is repeated to assess for any psychiatric diagnosis during the year of study participation and the BDI-II will be completed to check and record the participants' status at the end of the study. Changes in the treatment plan during the study participation are assessed and recorded. The Samsung Galaxy 5® smartwatch is returned to the study team and any final questions are answered. Note: MONDY is the name of the overarching project: “MONDY: Secure and open platform for AI-based healthcare apps”, see Funding information.

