To address RQII, i.e. “Can personal MS data predict the self-reported depressive symptom severity on a) the next day(s) and/or b) the next week(s)?“, we apply various machine learning techniques. Exploratory analyses investigate the predictability of depressive symptoms within individuals, using either classification or regression approaches. We compare idiographic models, which use data from individual patients, with nomothetic models based on data from all participants. Furthermore, we plan to examine whether multitask-learning methods [57] can enhance performance. Modern machine learning models, such as deep neural networks (DNNs), are validated against classical state-of-the-art methods, including boosted ensemble techniques [58], support vector machines [59], and autoregressive models [32] focusing on vector autoregressive (VAR) models and their analyses using forecast error variance decomposition (FEVD) and impulse response functions (IRF) specifically for idiographic approaches. Individual thresholds for high depressive symptom severity are derived from the data. Using eXplainable AI (XAI) methods, we evaluate the sensor technology component within iTD to understand the significance and impact of various MS features on the model's outcomes. This will help to identify the most relevant aspects of the MS data and clarify their influence on potential decision-making processes. Models based on data from all participants are validated using leave-one-subject-out cross-validation (LOSO-CV) [60,61], while within-subject models employ time-series cross-validation [62,63] and rolling back cross-validation [64].

For both RQ, sensitivity analyses will be conducted using different amounts of input data (e.g., 12 vs. 24 h of MS data, all AA vs. only MS data).

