### Strengths and limitations

2.1

A major strength of the proposed study protocol is the focus on intraindividual processes and the personalization of the data analysis approach. However, there are also some limitations to address: (1) We hope to achieve a very high data density for the individual participants through continuous data collection over the course of one year and constant monitoring of data completeness and quality by the study centre. Potential missing data might pose limitations on the success of the study though. We require daily and weekly self-reports from patients as an indicator of their depressive symptom severity, which bears a risk of non-compliance or fatigue with the study procedures. If patients were more non-compliant on days with stronger depressive symptoms, the prediction of these days with higher symptom burden might get very difficult as this represented an “out-of-sample” prediction in Machine Learning terms. (2) The performance of prediction models may vary across participants and the focus on the individual furthermore bears a risk of overfitting predictive models. Even when we collect contextual information from participants, the data might not fully represent the daily experiences and context of the person, which makes it possible that patterns are related to the specific context of data collection during the year and might not generalize to the life of individuals after participation in the study. (3) The current work is a pilot study for individualized long-term depression modelling. Given the heterogeneity of depression, the symptoms and patterns observed in the current, small sample may not be representative of the broader population of patients suffering from depressive disorders. This limits the generalizability of our findings, which will need to be validated in larger samples.

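### All one-year completers entered in a single autumn, so time since entry and season nearly coincide, and leave-one-subject-out validation of the pooled models cannot expose a link that arises from this

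*Protocol article*

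**What the plan says.** - **Calendar.** Trial status (1.3.3) states: "first patient in was September 27, 2023, last patient out was December 02, 2024". Design (1.1) sets repeated measurement "over the time of one year (365 days) within individuals", and the Fig. 1 caption adds: "The final appointment (V12) is conducted after 12 months of study participation".
- **Sample.** Section 1.2 gives the target size: "We aim to collect 10–12 complete case studies of adult patients with depressive disorders; allowing for some dropout, *N* = 15 participants will be included". Recruitment is at one Frankfurt department, with wider channels only as a fallback.
- **Entry rule.** Table 1 requires "Currently residual symptoms of depression (BDI-2 sum score ≥14" and concurrent treatment for the depressive illness.
- **Features.** Biosensors (1.4.3.1) lists accelerometer, steps, light and heart rate. Speech, app use and calls are recorded as well.
- **Validation.** Data analysis (1.6) says: "Models based on data from all participants are validated using leave-one-subject-out cross-validation (LOSO-CV". Within-subject models use time-series and rolling cross-validation instead. The same section compares idiographic with nomothetic models and uses explainable-AI (XAI) methods to rank sensor features.
- **Limitation.** Strengths and limitations (2.1) allows that "patterns are related to the specific context of data collection during the year" and may not carry over to patients' lives after the study.

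**The concern.** LOSO-CV protects against patterns peculiar to one patient. It does not protect against a time course that the training patients and the held-out patient share. If completers all start in the same autumn, a general fall in symptom scores after entry lines up with the same stretch of the calendar in each of them. Any feature with an annual cycle can then help to predict severity in a held-out patient even if it has no relation to that patient's mood. The bias has the same direction across patients, so pooling does not average it away.

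At stake are the nomothetic side of the comparison in research question II and the feature ranking. Light or activity could rank high because of the entry date. The stated limitation concerns generalization after participation. It does not say that season and time since entry cannot be separated within the data. The sensitivity analyses named in Data analysis (1.6) vary the amount and type of input, which does not bear on this.

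**Working it through.** **Step 1: entry window (figures from the article).** 27 Sep 2023 to 2 Dec 2024 is 432 days. The latest entry of a 365-day completer is 2 Dec 2024 minus 365 days = 3 Dec 2023. Window: 432 − 365 = 67 days (66 to 68, depending on how a year is counted). Dropouts could have entered later.

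**Step 2: does a fall after entry line up with day length?** Assumptions: latitude 50.1 N for Frankfurt, and a symptom course exp(−t/τ) with t in days since entry. Day length = (24/π)·arccos(−tan φ · tan δ), where φ is the latitude and δ the solar declination. Correlation of the two curves over the full 365 days:

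| Entry | τ = 14 | τ = 60 | τ = 90 | τ = 365 |
|---|---|---|---|---|
| 27 Sep | −0.12 | −0.53 | −0.64 | −0.77 |
| 30 Oct | −0.31 | −0.68 | −0.73 | −0.68 |
| 3 Dec | −0.40 | −0.62 | −0.58 | −0.37 |

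The full-year sign is negative throughout. The early phase differs: days still shorten for 85 days after a 27 Sep entry and for 18 days after a 3 Dec entry. Over the first 90 days with τ = 60, taking a cosine annual cycle with its minimum on 21 Dec, the correlation is +1.00 (27 Sep), +0.69 (30 Oct) and −0.83 (3 Dec).

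**Step 3: null simulation with no link between feature and mood.** All settings are assumptions:
- 12 patients, 365 days each, AR(1) noise with coefficient 0.5 and SD 1 in both series.
- Feature = s·(day length − 12.2)/2.8 + noise, with s = 0.3 or 0.7.
- Score = standardized exp(−t/T) + noise, with T varying between patients around τ = 30 to 365 days.
- Both series centred within person. Slope b = Σxy/Σx² from the other 11 patients. Held-out R2 = 1 − Σ(y − bx)²/Σy².

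| All patients improve | Mean within-person r | Mean LOSO R2 | Runs with mean R2 > 0 |
|---|---|---|---|
| Entry in the 67-day window | −0.10 to −0.28 | 0.01 to 0.08 | 100% |
| Entry spread over the year | about 0 | −0.001 to −0.005 | 13 to 20% |

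With autumn entry but no improvement trend, R2 is 0.

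**Step 4: dependence on a shared course.** Settings: τ = 90, s = 0.7, 12 patients, 67-day window. Patients who do not improve are given an equal and opposite worsening.

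| Share improving | 100% | 90% | 75% | 60% | 50% |
|---|---|---|---|---|---|
| R2, trend SD equal to noise SD | 0.076 | 0.046 | 0.013 | −0.004 | −0.007 |
| R2, trend SD half of noise SD | 0.030 | 0.017 | 0.005 | −0.001 | −0.004 |

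A further null simulation of the same kind gave about 0.04 with all improving, 0.008 at 75% and nothing at 60%.

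**Step 5: does a time-and-season benchmark separate the two cases?** In simulation, the R2 that the feature added over a benchmark of study day and an annual term was about 0 with no link, and about +0.07 with a true day-level link.

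**The case against.** The strongest reply has five parts.

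1. **Common recovery is not in the article.** A reader might infer that every patient recovers as the days lengthen and that LOSO-CV will therefore confirm false links. The documents do not support this. Management of suicidality (1.3.1) expects a phasic course with possible worsening, and the introduction describes chronic illness with residual symptoms. Step 2 also shows that the early months run from light to dark, with a sign that reverses within the window. This stands: the claim is conditional, and the word is can, not will.
2. **The effect is small and depends on its settings.** This stands. It needs both a mostly shared improvement and seasonal features, and the article gives no seasonality for any feature.
3. **The main aim concerns individualized models.** This stands. Those are not validated by LOSO-CV, although each of them also sees only one annual cycle. The point is limited to the pooled comparator and its feature ranking.
4. **A condensed article may leave trend and season terms to a fuller plan.** This is correct, and their absence is not the finding. The finding is that the stated accrual dates and the stated validation method together leave a shared confounder that this validation cannot show.
5. **The limitations already mention the year of collection.** This stands only in part. That text concerns generalization afterwards, not confounding within the data.

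**Conclusion.** The point holds in conditional form. The 67-day entry window follows from the article's own dates, and LOSO-CV cannot detect a confounder that the held-out patient shares. Whether this inflates pooled results depends on two things that the documents do not state: that most patients improve after entry, which selection on current symptoms under treatment makes plausible, and that some features follow the season. If both hold, the spurious LOSO R2 is about 0.01 to 0.08 in the simulations. It shrinks to about 0.01 when 75% improve and is gone when about 40% do not, with those patients modelled as worsening to the same degree. If they merely stayed level, the effect would fade more slowly. The documents do not show that false links will be confirmed, and the individualized analyses are outside this point. It is a cheap improvement to an exploratory analysis, worthwhile because a proof of concept may rest on small positive skill.

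**What to change.** **In Data analysis (1.6), for group-level models only:**
- Add a LOSO benchmark whose only predictors are study day (as a smooth term) and an annual or day-length term, fitted in the training patients. Both predictors are known in advance, so nothing leaks from the held-out patient.
- Report the skill that sensor features add over this benchmark, alongside the unadjusted skill.
- Base the group-level statement that behaviour predicts severity, and the XAI ranking of seasonal features, on the added skill.
- Do not detrend the held-out patient's PHQ scores with that patient's own full-year data. This would use future outcomes to define the target, and would strip slow change that weekly forecasting may need.

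**In Strengths and limitations (2.1):** state that all completers entered in one autumn, so season and time since entry cannot be separated.

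**Cost.** One more model, one more column of results and one sentence, with no new data. The downside is that genuine slow associations that follow the shared time course are credited to the benchmark, so the added skill will look less favourable. That is why both figures should be shown.

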### Measures

1.4

Three categories of data (clinical assessments and two types of AA data: self-report and MS) are collected and described below.

#### Clinical assessments

1.4.1

##### The structured clinical interview for DSM-5® (SCID-5)

1.4.1.1

The SCID-5 [38] is a semi-structured interview guide for making the major diagnoses in line with DSM-5 (Diagnostic and Statistical Manual of Mental Disorders, Fifth Edition [39]). It is administered by a trained mental health professional to assess inclusion and exclusion criteria for study participation at V0, and to assess any psychiatric diagnosis during the year of study participation at V12.

##### Beck Depression Inventory® (BDI-II)

1.4.1.2

The BDI-II [40] is a brief, self-report inventory designed to measure the severity of depression symptomatology. It is administered by a trained mental health professional at V0, V6, and V12. To assess the presence of residual depressive symptoms, a sum score of ≥14 is used as inclusion criterion.

##### McLean screening instrument for borderline personality disorder (MSI-BPD)

1.4.1.3

The MSI-BPD [41] was developed as a self-report screening measure for DSM-IV (Diagnostic and Statistical Manual of Mental Disorders, Fourth Edition) borderline personality disorder [42]. It is administered by a trained mental health professional at V0 with a cut-off score of ≥7 to exclude individuals with potential borderline syndrome.

#### Participant self-report

1.4.2

Daily (morning, evening) and weekly self-reports are assessed through the iTD-App. The exact wordings of all daily self-report items are shown in the Supplementary Material.

##### Daily self-report

1.4.2.1

In the morning and evening assessments, well-being (mood, tension, exhaustion, rumination) and sleep in the previous night are assessed. In the evenings, daily self-reported depressive symptom severity is assessed using the Patient Health Questionnaire-2 (PHQ-2 [43]), a very short measure assessing two core symptoms of depression (loss of interest/joylessness and feeling down/depressed/hopeless). Following previously established procedures [15,16], answers are given on a Visual Analogue Scale ranging from 0 to 10 with labelled endpoints (0 = never, 10 = all the time). Additionally, contextual information is queried to facilitate the interpretation of the data (substance use, medication, daytime activities).

##### Weekly self-report

1.4.2.2

The Patient Health Questionnaire-9 (PHQ-9, [44]) is used to assess the weekly self-reported depressive symptom severity. To this end, the original wording of the introductory sentence was changed to “Over the *last week*, how often have you been bothered by any of the following problems?“. The PHQ-9 is a short self-report measure of depressive symptoms that is able to detect changes in depression over time [45] and has been recommended as a general measure of depression severity by the DSM-5 [39]. Each item is rated on a four-point Likert scale ranging from 0 to 3, total scores range from 0 to 27. Higher scores indicate more severe depressive symptoms.

The Situational Self-Awareness Scale (SSAS, [46]) is used to assess weekly fluctuations in public and private self-awareness occurring at the time of self-monitoring during this study. Data can be used to clarify the relation between self-awareness, continuous self-monitoring, and depressive symptoms. The SSAS is sensitive to changes in self-awareness within individuals over time and across situations [46]. A German version is used which was created by two native German speakers using the double-translation and reconciliation procedure [47].

Additionally, participants are asked weekly about life events (“Were there any special events this week that concern you?“), with the option to enter a free text note in the iTD-App.

#### Mobile sensing

1.4.3

Objective parameters are generated by MS technology, connecting external biosensors to the iTD-App and by evaluating smartphone-internal sensors and the operating system.

##### Biosensors

1.4.3.1

Participants collect continuous data with portable sensors. A SAMSUNG Galaxy Watch5® is connected to the participant's smartphone via Bluetooth. The smartwatch includes advanced and reliable sensor combinations; the 3-axis accelerometer, motion sensor for step count, light sensor, and optical heart rate sensor are used and recorded by the iTD-App. Data from the Samsung smartwatch is obtained via the Samsung Privileged Health SDK (Tracking Service) and WearOS sensors, temporarily stored on the watch's local database, then iteratively transferred to the smartphone's local database. The data is subsequently uploaded to the MONDY platform, with no involvement of external providers.

